### Aims and Research Questions

Short-term (10-week after intervention start) and long-term efficacy and effectiveness (24-week and 38-week after intervention start) of a digitally supported mindfulness intervention for nurses and nursing trainees will be investigated. As the efficacy and effectiveness of an intervention are likely influenced by participants’ degree of adherence to the instructions and acceptability, we will investigate variables that may increase or decrease the likelihood of participant adherence and acceptability. The research questions are as follows:

Relative to a wait-list control group (WCG), does access to a digitally supported mindfulness intervention improve subjective health- and work-related outcomes among nurses and nursing trainees in acute inpatient care settings randomized to the intervention group (IG) at 10 weeks after allocation?Relative to scores observed at baseline, does access to a digitally supported mindfulness intervention improve subjective health- and work-related outcomes among nurses and nursing trainees in acute inpatient care settings at 10, 24, and 38 weeks after intervention start? To what degree do app-based minutes of meditation predict each of our outcomes?Which variables are associated with adherence to a digitally supported mindfulness intervention at 10, 24, and 38 weeks after the intervention starts among nurses and nursing trainees in acute inpatient care settings?Which variables are associated with the acceptability of a digitally supported mindfulness intervention at 10, 24, and 38 weeks after the intervention starts among nurses and nursing trainees in acute inpatient care settings?

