##### Adherence

Adherence to the instructions for using the digitally supported mindfulness intervention will be operationalized as daily meditation. The frequency of meditation practice (app-based and non–app-based meditation) will be recorded based on the following answer options: several times per day, daily, 4 to 6 times per week, 1 to 3 times per week, less than 1 time per week, or never.

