#### Statistical Methods

##### Overview

Analyses will be conducted using *SPSS Statistics* (IBM)*.* For tests involving our primary outcome variable, we will set an α level of .05. For all other analyses, to reduce α-error inflation, we will interpret the obtained *P* values descriptively, meaning all other analyses will be exploratory and are designed to observe trends and not to identify significance.

Patterns of missing data will be assessed, and adequate data imputation techniques such as multiple imputation with *SPSS Statistics* (IBM) will be applied. Before doing so, we will assess the percentage of missing data. We will also use Little's Missing Completely At Random test to determine patterns of missing data (ie, missing completely at random vs not missing at random).

We will reverse code 3 outcomes [32,38,40] so that a higher score indicates health improvement. For example, the scale assessing burnout [40] is designed to indicate that a score of 1 indicates a rather minuscule risk of burnout, whereas a score of 100 indicates the highest risk of burnout, meaning that greater scores indicate a worsening of symptoms. After recoding this variable, greater scores will reflect a lower risk of burnout (ie, an improvement in symptoms).

Effectiveness will be evaluated using an intention-to-treat (ITT) approach; all randomized participants will be included in our analyses [45].

Efficacy will be evaluated using a per-protocol (PP) approach; only study completers who report adherence will be included in our analyses.

Several analyses will be used to address the research questions. To ensure that our randomization has worked as intended, we will assess for between-group differences for relevant participant characteristics and, if needed, adjust the following analyses. For research questions 2, 3, and 4, we will create a pooled data set merging the data of the IG and the WCG. We will merge the data of the 2 groups so that IG T0 data will be combined with WCG T1 data, and IG T1 data will be combined with WCG T2 data, as described in Textbox 1. For research questions 3 and 4, relationships between variables will be examined using correlation analyses (Pearson correlation coefficient, eta quotient, and chi-square tests). If violations of the assumptions associated with any of the analyses are detected, alternative tests will be used.

Data pooling procedure.

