**Newly pooled data set and data included**
Participant data baselineCases of the intervention group at time point 0Cases of the wait-list control group at time point 1Participant data 10 weeks after intervention startCases of the intervention group at time point 1Cases of the wait-list control group at time point 2Participant data 24 weeks after intervention startCases of the intervention group at time point 2Cases of the wait-list control group at time point 3

##### Research Question 1

We will present the ITT sample’s baseline characteristics and test for detectable between-group differences. For continuous variables, mean, SD, median, minimum, and maximum values will be calculated. For categorical variables, frequencies (absolute and percentages) will be calculated.

To evaluate the effectiveness and efficacy of the 10-week access, we will create one difference score per group for each of our outcomes assessed at T0 and T1. Using a 2-sample *t* test, we will test whether significant differences exist between the 2 difference scores in the IG and WCG. We will perform this for the ITT and PP sample. If *P*<.05, Cohen *d* will be calculated.

##### Research Question 2

To evaluate long-term effectiveness and efficacy, we will use the pooled data set. To analyze the effect of time on our variables of interest, a repeated-measures ANOVA will be conducted for each of our outcomes. As only participants randomized to the IG will be assessed at 38 weeks after allocation, long-term efficacy within this group will be examined using an additional repeated-measures ANOVA.

Using a PP approach, we will examine the relationship between *app-based minutes of meditation* and each previously calculated difference score using the pooled data set. Linear regression will be performed to examine the relationship between the minutes of meditation and each outcome. The baseline scores of primary and secondary outcomes will be entered into the model as additional explanatory variables to control for individual differences before the start of the intervention.

##### Research Question 3

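### The regression of outcome change on app minutes is specified only in daily meditators, which is narrower than the research question and probably costs much of the sample

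*Protocol article*

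**What the plan says.** The question, under Aims and Research Questions, is "To what degree do app-based minutes of meditation predict each of our outcomes". It names no subgroup.

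The analysis, under Research Question 2, reads "Using a PP approach, we will examine the relationship between" app minutes and each difference score, in the pooled data set and by linear regression. It continues: "The baseline scores of primary and secondary outcomes will be entered into the model as additional explanatory variables". No version in all users is given.

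The PP set is defined in the Overview of the statistical methods: "Efficacy will be evaluated using a per-protocol (PP) approach; only study completers who report adherence will be included in our analyses". The Adherence section says: "Adherence to the instructions for using the digitally supported mindfulness intervention will be operationalized as daily meditation". Its answer scale is "several times per day, daily, 4 to 6 times per week, 1 to 3 times per week, less than 1 time per week, or never", and the recording covers both kinds of practice: "The frequency of meditation practice (app-based and non–app-based meditation) will be recorded".

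The Intervention section leaves frequency and duration to the participant and plans no standardized reminders to meditate. Research Questions 3 and 4 relate intensity of use to adherence and acceptability in the intention-to-treat (ITT) sample. The Sensitivity Analyses section plans a complete-case repeat for research questions 1 and 2 and does not mention adherence.

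**The concern.** A dose-response question is best informed by people across the whole range of dose. Here the model is fitted only after selecting people by how often they say they practise, which is closely related to how many minutes they accumulate. On the six-level scale, the four levels from 4 to 6 times per week down to never fall outside the analysis. Since use is free and unprompted, answers at those levels are to be expected.

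Two things are at stake. First, the result answers a narrower question (among daily meditators who completed, do more minutes go with more improvement?) than the one posed. Second, the sample shrinks, so a flat or unstable slope is likely even if minutes matter, and could be misread as showing that the amount of practice is unimportant.

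**Working it through.** **Plan's own figure.** The document gives no sample size, power or expected spread for this regression. Its only calculation is for the between-group t test (Sample Size section: d = 0.67, two-sided alpha .05, power .80). That reproduces: the noncentral t gives 36 per group (power 0.8005), and 36 / 0.8 = 45 after 20% dropout. It has no bearing on the regression.

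**Inputs from the document.** 79 randomized (Results); 20% assumed dropout (Sample Size); earlier trials' dropout of about 25% to 48% (Introduction).

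**Assumptions, not in the document.** A full-sample correlation of 0.30 between minutes and outcome change; 50% or 25% of completers meditating daily; every completer reporting minutes.

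**Step 1, sample.** Completers: 79 × 0.80 = 63.2, about 63. PP at 50%: 31.6, about 32. PP at 25%: 15.8, about 16.

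**Step 2, precision with the correlation held at 0.30 (no range restriction).** With m = atanh(r) × √(n − 3), two-sided power = Φ(m − 1.96) + Φ(−m − 1.96). The smallest detectable r at 80% power = tanh[(1.96 + 0.842) / √(n − 3)]. atanh(0.30) = 0.3095.

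| Set | n | m | Power for r = 0.30 | Smallest detectable r |
|---|---|---|---|---|
| All completers | 63 | 2.40 | 0.67 | 0.35 |
| PP, 50% daily | 32 | 1.67 | 0.38 | 0.48 |
| PP, 25% daily | 16 | 1.12 | 0.20 | 0.65 |

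**Step 3, adding range restriction.** If minutes were normal and daily meditators were exactly the top users, the SD ratio u (PP to all) would be 0.60 for the top 50% and 0.49 for the top 25%. With r′ = r·u / √[1 + r²(u² − 1)], r′ is 0.19 or 0.15, and power is 0.17 (n = 32) or 0.09 (n = 16).

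**Step 4, does step 3 depend on the distribution?** Yes. For the top 25% by minutes, u is 0.49 (normal), 0.95 (log-normal, log-SD 0.5), 1.00 (exponential) and 1.44 (log-normal, log-SD 1). Simulations that built minutes from assumed weekly frequency and session length gave PP-to-all variance ratios from 0.07 (everyone exactly once daily, 7 to 10 minute sessions) to 2.43 (varied session lengths, some practising several times a day). Power in the PP set was lower in every scenario: 0.04 to 0.45, against 0.67 in 63.

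**Step 5, how much of the sample goes?** To keep half of the 79, the daily share among completers must be at least 0.5 / (1 − dropout): 62.5% at 20% dropout, 67% at 25%, 96% at 48%.

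**The case against.** A reader might infer that PP removes most of the variation in minutes. The document does not support that. PP selects on self-reported frequency, counts non-app practice, includes people practising several times a day, and leaves session length free. As step 4 shows, the spread could shrink sharply, stay the same or grow.

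A reader might also state as fact that most participants are lost. That is likely on the document's dropout figures, but it rests on an adherence rate given nowhere.

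A third tempting reading is that every model carries about 12 baseline scores, leaving 16 − 12 − 1 (minutes) − 1 (intercept) = 2 residual degrees of freedom at n = 16. That needs both the most literal reading of the covariate sentence and the 25% assumption. The sentence can equally mean that each model takes the baseline of its own outcome.

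Three further objections have weight. If the linear model is correct, selecting on a predictor costs precision but does not bias the slope, and the planned estimate is a slope, not a correlation. The PP choice follows the article's definition of efficacy as the effect when the protocol is followed, so minutes among adherers is a coherent question. And all analyses other than primary-outcome tests are declared exploratory.

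These points limit the size of the problem. They leave two things standing: the mismatch with the stated question, and the loss of sample. The complete-case analysis does not clearly repair either, as it does not say that non-adherers return to the regression.

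**Conclusion.** The point holds in this form. The minutes regression is specified only among completers reporting daily meditation, while the question it serves has no such limit. This cuts off low and zero users, makes the slope describe adherers only, and probably excludes a large part of the sample. The loss of variation in minutes cannot be determined.

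Under the stated assumptions, power for a correlation of 0.30 falls from 0.67 to between 0.20 and 0.38 from sample loss alone, and to between 0.09 and 0.17 if minutes are normal and adherers are the top users. The conclusion takes the daily criterion of the Adherence section as the one meant in the PP definition. Severity is modest: most of these models are exploratory, although the one for PSS-10 could be read as a primary-outcome test at alpha .05.

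**What to change.** Make the main minutes regression an analysis of all participants in the pooled set who were given access and have a follow-up score and minutes data. Enter those who never activated the access code (activation is already recorded) as 0 app minutes. State that each model adjusts for the baseline of its own outcome. Keep the PP regression as a sensitivity analysis, and report the slope as an association because dose is self-chosen.

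The cost is a change of wording, using variables already planned. There is a small downside. Including low and zero users adds self-selection confounding, since engaged and unengaged people may differ in other ways. People who meditate without the app are placed at zero app dose. Minutes are self-reported and may be missing, so the gain in sample may be smaller than the illustration suggests. Showing both versions side by side lets readers judge this.

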#### Sample Size

On the basis of the available literature on interventions similar to ours, we assumed a medium effect size (Cohen *d*=−0.67) in reducing stress measured by PSS-10 [44]. The sample size calculation was conducted for a 2-tailed *t* test with a significance level of α=.05 and a power of β=.80 (comparison between the IG and the WCG). Sample size calculations using the G*Power tool (Düsseldorf University) suggested that 72 participants (36 in the IG and 36 in the WCG) are needed to detect an effect size of 0.67. Assuming a dropout rate of 20%, 18 additional participants were required (45 per group).

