Using the pooled data set, to determine which variables are associated with adherence at 10 weeks and 24 weeks after intervention start, we will examine the correlations between the variable *frequency of meditation practice* and participants’ baseline characteristics, acceptability, and intensity of intervention use using the ITT sample. To assess adherence at 38 weeks after the intervention, analyses will be conducted using the ITT data set of the IG.

##### Research Question 4

Using the pooled data set, to determine which variables are associated with acceptability at 10 weeks after the intervention start and 24 weeks after the intervention start, we will examine the correlations between the variable of *perceived usefulness* (acceptability) and participants’ baseline characteristics and intensity of intervention use using ITT sample. To assess acceptability at 38 weeks after the intervention, analyses will be conducted using the ITT data set of the IG.

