Detection bias may occur as blinding of participants is not possible, given the nature of the study. Although the study design is not communicated to the participants, the participants are to be likely aware of which group they have been randomized to. There may be a risk of social desirability as the effects will be evaluated based on subjective reports, including the frequency and intensity of digitally supported mindfulness intervention use, and no biological parameters will be collected. To reduce detection bias, all questions were tested among members of the target group before the start of the study, and all outcome measures were validated in previous studies. Evaluations of the psychometric properties of our primary outcome, the PSS-10, in different countries report a Cronbach α of .78 to .91, with good test-retest reliability [57]. PSS-10 scores correlate significantly with cortisol levels and constitute an objective measure of cumulative stress [58]. We will also seek to reduce the risk of social desirability by informing participants of the pseudonymization and anonymous publication of the data and by conducting data collection without in-person contact. In addition, we will not use participant data collected via the app but will allow participants to report data collected by the app. We refrained from tracking app use and the duration of use for privacy reasons. Not tracking app use may increase rapport, as participants will not feel monitored while using the app. Finally, the item with which we assessed gender may present a limitation as the German language uses the same term for sex assigned at birth and gender identity; thus, we cannot be certain whether participants reported their sex or their gender.

Performance bias will be reduced by using a standardized intervention; however, COVID-19–related differences may occur, as the WCG will receive the intervention at a later time.

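### The pooled regression on app minutes and the pooled correlations of time-varying variables in Research Questions 3 and 4 combine two start periods 14 weeks apart without an arm term

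*Protocol article*

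**What the plan says.** The Statistical Methods overview announces a common data set for the last three research questions: "we will create a pooled data set merging the data of the IG and the WCG". The data pooling box gives the alignment: intervention-group T0, T1 and T2 are stacked with wait-list T1, T2 and T3. The Design and Participant Timeline sections put the two starts of access 14 weeks apart.

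Three analyses of this pooled set matter here.

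- **Research Question 2, minutes regression.** It is per-protocol, with difference scores regressed on app-based minutes. The covariates are named: "The baseline scores of primary and secondary outcomes will be entered into the model as additional explanatory variables". The stated purpose is to control for individual differences before the intervention.
- **Research Question 3.** Practice frequency is correlated with baseline characteristics, acceptability and intensity of use. The opening words fix the data and the time points: "Using the pooled data set, to determine which variables are associated with adherence at 10 weeks and 24 weeks after intervention start".
- **Research Question 4.** Perceived usefulness is correlated with baseline characteristics and intensity of use at the same two time points.

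For Research Questions 3 and 4 the overview lists Pearson correlation, eta and chi-square. These are two-variable measures without a covariate. No arm, start-period or calendar term is named for any of the three analyses. Under Strengths and Limitations the article allows that pandemic-related differences are possible; the reason it gives is: "as the WCG will receive the intervention at a later time".

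**The concern.** In the pooled set, arm and start period are the same thing. T0 closed and randomization took place at the end of October 2021. The intervention group's pooled baseline is therefore autumn 2021. The wait-list group's is T1, 10 weeks after allocation (about January 2022), with access from about February 2022.

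Randomization balances fixed traits between the arms. It does not balance quantities measured in different calendar periods, or after a wait. These include minutes, practice frequency, perceived usefulness, other measures of use, score change, recent hours worked, patient contact and COVID-19 care.

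If two such quantities differ between the start periods, they are associated in the stacked data even when no such relation exists between persons within either arm. Shifts in opposing directions can weaken a real relation. At stake are the minutes slope and the lists of variables reported as associated with adherence and acceptability, which the article wants to use to inform implementation.

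**Working it through.** **The plan's own figure.** The article gives no figure for the pooled analyses. Its only sample-size figure is for the two-arm t test and it reproduces: d = 0.67, two-sided α = .05 and power .80 give n = 35.96, so 36 per arm; 36/(1 − 0.20) = 45 per arm. It has no bearing on this point.

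**Inputs.** 40 and 39 randomized, N = 79 (Results). The arm shifts *d* and *g* in the two variables, in within-arm SD, are assumptions. I take the wait-list difference score in the pooled set to run from T1 to T2, because the T0-to-T1 score of Research Question 1 precedes that arm's access.

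**Formula.** With a share *p* of participants in one arm, the pooled covariance is the within-arm covariance plus p(1 − p)·d·g. Here p(1 − p) = (40/79)(39/79) ≈ 1/4. With no within-arm relation,

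r = (dg/4) / √[(1 + d²/4)(1 + g²/4)].

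- 0.2 and 0.2 SD: 0.01/1.01 = 0.010
- 0.5 and 0.5 SD: 0.0625/1.0625 = 0.059
- 0.8 and 0.8 SD: 0.16/1.16 = 0.138
- 1 and 1 SD: 0.25/1.25 = 0.200
- 0 and 0.5 SD: 0

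**Masking.** With a true within-arm r of 0.30 and shifts in opposite directions, r = (0.30 − dg/4)/√[(1 + d²/4)(1 + g²/4)]. For 0.5 SD this is (0.30 − 0.0625)/1.0625 = 0.22. For 0.8 SD it is (0.30 − 0.16)/1.16 = 0.12.

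**Simulation of the correlation** (20,000 runs, no within-arm relation; N = 63 is 79 less 20%):

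| Shifts (SD) | Pooled r | P<.05, N = 79 | P<.05, N = 63 |
|---|---|---|---|
| 0 / 0.5 | 0.00 | 5.0% | 5.2% |
| 0.2 / 0.2 | 0.01 | 4.9% | 5.1% |
| 0.5 / 0.5 | 0.06 | 8.0% | 7.4% |
| 0.8 / 0.8 | 0.14 | 23.6% | 19.5% |
| 1 / 1 | 0.20 | 43.9% | 36.3% |

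Adjusted for arm, r is about 0 and P<.05 occurs in 4.7% to 5.3% of runs throughout. The rejection rate falls with N; the spurious r does not depend on it.

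**Do the planned baseline scores remove the bias?** I regressed simulated change on minutes and the outcome's own baseline (5,000 runs, N = 79, no true slope, minutes and follow-up score both shifted). Without arm the mean slope was 0.047, 0.110 and 0.162 for shifts of 0.5, 0.8 and 1 SD. When the baseline itself also differed by 0.5 SD, it was 0.043, 0.106 and 0.155. With arm in the model the slope was within 0.002 of zero in every case. Baseline adjustment therefore leaves the bias in place.

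**The case against.** The strongest reply concerns weight, and much of it stands.

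- **The shifts are not in the documents.** The bias is negligible at 0.2 SD, small at 0.5 SD, and absent if only one variable moves. The 0.8 SD case needs both variables to move by more than the intervention effect the trial itself assumes (0.67). This stands.
- **P values are mostly descriptive.** The overview reserves α = .05 for tests involving the primary outcome and calls the rest exploratory. Research Questions 3 and 4 fall in the rest; at most the minutes regression on PSS-10 change falls under the α. This stands, and rejection rates are secondary here. A descriptive label does not remove bias from a slope or a correlation.
- **The regression sample is smaller than 79.** It is limited to completers who report adherence. This stands. It lowers the rejection rates but not the bias for a given shift.
- **Between-period variation can be genuine signal.** If heavier COVID-19 care reduces practice, adjusting for arm discards part of that relation. This stands and is a reason to show both estimates.
- **The overview allows adjustment if needed.** This stands only in part. The trigger is a check that randomization worked, based on participant characteristics. A difference between start periods is not a failure of randomization.

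The complete-case sensitivity analysis adds no arm term either.

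A reader might infer more than the text bears: that the article expects the start periods to differ, or that every pooled correlation is contaminated. The article says only that differences may occur. Correlations with fixed traits such as age, gender or prior meditation experience are not biased in expectation, because randomization makes those traits independent of arm.

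**Conclusion.** The point holds as a conditional risk of bias in the estimates. The minutes regression and the 10- and 24-week correlations among time-varying variables leave start period uncontrolled, and the planned baseline covariates do not replace it. The spurious correlation is about 0.01 to 0.14 for assumed shifts of 0.2 to 0.8 SD in both variables with no within-arm relation. A true 0.30 could fall to between 0.22 and 0.12 under opposing shifts of 0.5 to 0.8 SD. Whether shifts of that size will occur cannot be known from the documents.

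It would be wrong to conclude that these analyses carry a false-positive rate of 20% or more. That needs large shifts in both variables, and a significance reading that the plan does not make for Research Questions 3 and 4. The randomized comparison at 10 weeks (Research Question 1) and the 38-week analyses, which use the intervention group alone, are not affected. The change is worth making because it is nearly free, not because serious bias has been shown.

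**What to change.** Add arm (start period) as a covariate in the pooled regression of outcome change on app-based minutes. For the pooled 10- and 24-week associations in Research Questions 3 and 4 that involve time-varying variables, report arm-adjusted (partial) or arm-stratified estimates next to the planned unadjusted ones, so that a reader can see how much rests on the start period. Leave the fixed-trait correlations and the 38-week analyses as they are.

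The cost is one degree of freedom in each adjusted analysis and a sentence or two in the analysis plan. Arm is known for every participant, so no new data are needed.
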